#### Sample Size and Power

Given the low rates of homework completion in research to date, we expect that the app will have at least a moderate effect on homework completion compared with the no-app group [28,35,36]. A power calculation, based on a comparison between 2 groups (app vs no-app) across 4 occasions (pre, post, follow-up 1, follow-up 2) for a single measure, indicates that a sample size of 35 for each group would provide power of 0.84 to detect a moderate effect size for homework completion at α = .05. To allow for dropouts [98], we will recruit 100 youth between 12 and 18 years of age (10 per group at each site). As noted earlier, treatment dropout rates can be substantial and adherence to homework is often quite low. This has been taken into account in calculating the sample size. The expectation is that compliance will be greater for the app than the no-app group. Based on previous research with youth [98], we expect a 10% rate of attrition at each of the 2 follow-ups.

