##### Treatment Outcomes

For exploratory purposes, we will examine group differences in treatment outcomes. Group differences in anxiety and depression will be analyzed for both dichotomous (diagnosis) and continuous (symptom severity) measures. For each diagnosis (presence vs absence), chi-square tests will be performed comparing the number of youth meeting criteria for diagnosis at pre versus post, pre versus follow-up 1, and pre versus follow-up 2. For each of the continuous measures of symptom severity, following the recommended approach for trials with pre, post, and follow-up measures [115], a repeated measures multivariate analysis of the covariant will be performed in which the between factor is group (app vs no-app) and the within factor is time (pre, post, follow-up 1, follow-up 2), to compare group and time effects and interactions between group and time, using the pretreatment value as a covariate. Where significant effects are found, simple contrasts will be conducted to ascertain where the significant differences lie. Group differences in maladaptive cognitions (overall score) and quality of life (overall score), will be analyzed in the same way. Effect sizes will be calculated comparing the effects of app vs no-app on each of the outcomes. Analyses will also be performed to establish clinical significance and the reliable change index [116]. Subgroup analyses will explore differences in the app’s impact on treatment outcomes as a function of test site and gender.

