If the analyses reveal significant group differences in treatment outcomes, additional exploratory analyses will be performed to aid interpretation of the data. To explore whether better homework completion (greater quantity and/or quality) or something unique about the mobile technology is most likely responsible for group differences in treatment outcomes, we will examine associations between homework completion and treatment outcomes separately for the 2 groups. Mobile devices may increase patient engagement and empowerment [1,117] and reduce concern about the perceived stigma associated with receiving treatment [118], resulting in beneficial effects on treatment that are independent of homework completion. Accordingly, regression analyses (ordinary least squares, logistic) would be performed to predict each of the dichotomous (diagnosis) and continuous (symptom severity) outcomes at posttreatment, follow-up 1, and follow-up 2 from measures of homework completion, controlling for the pretreatment value of the outcomes. A finding of group differences in the strength of associations between homework completion and treatment outcomes would suggest that an improvement in homework completion is not the only mediator of app effects on treatment outcome.

Finally, if treatment outcomes are better for the app compared with the no-app group, exploratory mediation analyses will be performed for the app group to assess whether homework completion (quantity, quality) affects treatment outcomes indirectly through support for learning (ratings of how much the app supports access to assignments, memory and understanding of lessons, motivation to practice, coaching and suggestions, self-monitoring of symptoms and changes, review of homework). To test for mediation, we will perform tests of indirect effects using a regression-based path-analytic approach [119,120].

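### The homework-outcome analyses run only if symptoms differ significantly between arms, a condition their question does not need and this trial is not sized to meet

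*Protocol article*

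**What the plan says.** The Treatment Outcomes section opens by setting the status of everything in it: "For exploratory purposes, we will examine group differences in treatment outcomes". Each continuous symptom measure gets a repeated-measures analysis "to compare group and time effects and interactions between group and time, using the pretreatment value as a covariate". The list is then extended: "Group differences in maladaptive cognitions (overall score) and quality of life (overall score), will be analyzed in the same way". Diagnoses are tested by chi-square, described as comparing pretreatment with each later time.

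Two conditions follow. The first controls regressions of each outcome, at posttreatment and both follow-ups, on homework completion, with associations examined separately in the two arms: "If the analyses reveal significant group differences in treatment outcomes, additional exploratory analyses will be performed to aid interpretation of the data". The second is worded differently: "if treatment outcomes are better for the app compared with the no-app group, exploratory mediation analyses will be performed for the app group". That mediation analysis asks whether homework acts on outcome through ratings of support for learning, in app users only.

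Under Sample Size and Power, the only power statement concerns homework completion: 35 per group would "provide power of 0.84 to detect a moderate effect size for homework completion at α = .05".

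**The concern.** The introduction rests the case for the app on the link between doing homework and getting better. The regressions are the plan's own examination of that link in this sample. They are carried out only if a different and weaker comparison, the difference in symptoms between arms, reaches significance.

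An association within an arm can exist, and can be estimated, whether or not the arms differ. An indirect effect likewise does not require a significant total effect. The stated condition therefore selects on something that says little about the question.

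At stake is whether the mechanism is examined at all when the app works modestly through homework, or whether the decision to examine it turns on a chance result among many outcomes. Which of these is the greater risk depends on how the condition is read.

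**Working it through.** **The plan's own figure.** For 2 groups and 4 occasions, the between-group F test has noncentrality N f² m / (1 + (m − 1)ρ). The article gives neither f nor ρ. With N = 70, m = 4 and a conventional moderate f = 0.25, ρ = 0.32 gives 70 × 0.0625 × 4 / 1.96 = 8.93 and power 0.838. The stated 0.84 is thus reachable with ρ near 0.32, but it is power for homework. No figure is given for any treatment outcome.

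**Reading 1: outcome by outcome.** Assumptions not in the article: the moderate homework effect is 0.5 SD; it reaches symptoms only through homework; the homework-outcome correlation r is 0.2 to 0.4; testing is two-sided at 0.05. The between-arm effect on an outcome is then d = 0.5r. Power comes from the noncentral t with SE = √(2v/n) and n = 50 per arm (100 recruited). The variance factor v is 1 unadjusted, 1 − ρ² adjusted for baseline at one occasion, and (1 + 2ρ)/3 − ρ² for the baseline-adjusted mean of three later occasions with a lasting effect.

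Example at r = 0.4 (d = 0.20) and ρ = 0.6:
- Unadjusted: SE = √(2/50) = 0.20, noncentrality 1.00, power 0.168.
- One occasion: v = 0.64, SE = 0.16, noncentrality 1.25, power 0.236.
- Mean of three: v = 0.373, SE = 0.122, noncentrality 1.64, power 0.367.

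| r | d | Unadjusted | One occasion, ρ = 0.6 | Mean of three, ρ = 0.6 |
|---|---|---|---|---|
| 0.2 | 0.10 | 8% | 10% | 13% |
| 0.3 | 0.15 | 11% | 15% | 23% |
| 0.4 | 0.20 | 17% | 24% | 37% |

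Over ρ = 0.5 to 0.7 the last two columns span 9-28% and 12-43%. With 35 per arm and ρ = 0.6 the three columns run 7-13%, 8-18% and 10-27%.

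Compare the association the plan wants to examine within one arm of 50. By Fisher's z, power is about Φ(√47 · atanh r − 1.96). For r = 0.2, 0.3 and 0.4 this is Φ(−0.57), Φ(0.16) and Φ(0.94), or 28%, 56% and 83%. The controlling test is weaker than the analysis it controls at each r, even in the most favourable column.

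On this reading the false opening is small. Two tests per outcome give at most about 1 − 0.95² = 10%.

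**Reading 2: any significant test.** Counting from the Measures and Sample Characteristics sections: Achenbach internalizing and externalizing by youth and caregiver (4), MASC-2 by youth and caregiver (2), CDI-2 (1), maladaptive cognitions (1) and quality of life (1) make 9 scores. A group and a group-by-time test on each makes 18 tests. If independent, 1 − 0.95¹⁸ = 60%, or 1 − 0.95⁹ = 37% for group effects only. Simulation under no effect (50 per arm, between-score correlation 0.3 to 0.7, correlation across occasions 0.5) gives:
- Any group or group-by-time test significant: about 36-56%.
- Any group main effect significant: about 20-35%.
- Any group main effect significant and favouring the app: about 10-18%.

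The last line applies to the second condition only if it is taken to mean a significant benefit.

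On the same reading, a real benefit shared by all nine scores (d = 0.10 to 0.20, 50 per arm) satisfies the first condition in about 60-84% of trials. Varying the between-score correlation from 0.3 to 0.7 widens that to about one half to nine-tenths.

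**Selection and slopes.** With a true homework-outcome slope of 0.30, the average estimate is 0.300 over all simulated trials and about 0.291 among those with a significant group difference.

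**The case against.** The strongest defence is that the first condition suits its stated purpose. The regressions are introduced to explain group differences in outcome, and with no difference there is nothing to explain. Everything involved is labelled exploratory. The article condenses a fuller plan, so which outcome or test counts may be fixed there. That last point stands: the silence on the trigger is not the finding. What remains is that the article does state a significance condition, and that the homework-outcome association has value of its own, which the article's rationale asserts. The exploratory label limits what may be claimed; it does not make the condition a useful one.

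Four stronger inferences are tempting, and the article does not support them.

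- A reader might infer that the plan usually chases chance differences and also usually misses real ones. These belong to different readings. If any test counts, a shared real benefit often satisfies the condition. If outcomes are taken singly, false opening is about 10% per outcome. The article does not say that any test counts.
- A reader might put the chance rate at 64-85% by adding six diagnoses at three times. That needs between-arm diagnosis tests, and the chi-square tests as written compare times.
- A reader might treat the second condition as another significance rule. It asks only for better outcomes, and the mediation it controls is not an app-to-homework-to-outcome path.
- A reader might expect the estimates carried forward to be inflated by selection. The within-arm slopes are not.

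**Conclusion.** The point holds in a limited form. A significant between-arm difference is the wrong condition for analyses of how homework relates to outcome, and the trial was not sized to detect one.

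Taken outcome by outcome, a homework-carried benefit would usually leave the regressions undone: about 8-17% power unadjusted, 10-24% adjusted at one occasion, and up to about 40% with three occasions averaged. Taken as any test on about nine scores, chance alone satisfies the condition in roughly 36-56% of trials, or 20-35% on main effects only. Neither reading serves the question well.

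The sizes rest on assumed values for the homework effect, r, the correlations and the score count. With r of 0.5 to 0.6, per-outcome power over one or three occasions reaches 22-76%, so the miss is not certain. Every analysis affected is exploratory and the confirmatory comparison of homework completion is untouched. This is an optional improvement, not a flaw in the main inference.

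**What to change.** In the Treatment Outcomes section, remove the significance condition and run the homework-outcome and indirect-effect analyses whatever the group tests show. Fix a short list of outcomes in advance, for example MASC-2 and CDI-2 at posttreatment, and report exploratory estimates with confidence intervals. If a condition is kept, tie it to one named outcome and one named test, so that it is met in about 5% of trials when there is no effect.

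The cost is a sentence or two of wording and a few regressions on data already collected. The one downside is that mechanism estimates will also appear when no outcome differs between arms; the exploratory label and the intervals deal with that.

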### Support for Practice and Learning

Reflecting homework’s critical importance for the success of treatment, there is a direct association between homework completion and outcomes of CBT for anxiety or depression across a wide age range [28,31-34]. However, rates of homework completion are uniformly low across the age spectrum. Studies of adolescents in CBT for depression show that completion rates hover at approximately 50%, are highly variable, and tend to decline across sessions [28,35,36]. These findings may be partly attributable to insufficient support for practice and learning during the interval in between therapy sessions. Although the guidelines for administering homework are intended to ensure that practice occurs, much depends on the patient’s ability to continue practicing without the support that was provided during the treatment session. Whereas in-session learning occurs with the help of a therapist who provides encouragement, feedback, and problem-solving support, learning outside the session is a self-directed effort. The absence of the therapist’s support during the intervals between sessions may jeopardize the conduct of homework assignments.

Consistent with this interpretation, adolescents’ reflections on CBT homework suggest that they experience insufficient support for doing homework. In a CBT program for depression [37], adolescents regarded homework as important, but reported not always completing the assigned exercises because they did not feel motivated or found it too time-consuming. In another CBT program for depression, which consisted of a computerized program designed as a self-help computer game [38], adolescents gave various reasons for not completing homework, including lack of interest and not having a helpful resource. These findings suggest that homework as traditionally administered provides insufficient support for learning. Rates of homework completion may improve if greater support were provided. Adolescents especially are likely to benefit from enhanced support. Adolescence is a period of ongoing cognitive development involving growing understanding of abstract concepts relevant to CBT, and thus a time when support for learning is likely to be particularly important [39].

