### The Role of Mobile Tools

Mobile tools have the potential to facilitate many of the treatment processes involved in CBT [2,40]. In particular, given the essential role of homework in CBT, they have been conceptualized as a means by which the therapy setting can reach beyond the clinic to the patient’s everyday environment [41]. A mobile homework app may support learning between sessions in numerous ways, including making homework materials accessible and easy to keep track of; aiding memory and understanding of the lesson learned during the treatment session; providing coaching and suggestions (eg, through a help function); promoting intrinsic motivation (eg, through goals and challenges, rewards, feedback on progress [42,43]); facilitating self-monitoring of symptoms and changes (eg, through visual displays); and enhancing homework review and troubleshooting (eg, by summarizing results for discussion). In summary, mobile delivery of homework may provide a means of supporting the continuation of learning during the intervals in between treatment sessions.

The purpose of the proposed research is to design and evaluate a mobile CBT homework app that provides a support system for young people in therapist-led treatment for anxiety and/or depression. We expect that the app will improve homework completion by supporting learning; that is, by facilitating access to assignments, memory and understanding of lessons, motivation to practice, self-monitoring, and review of homework results. Given the impact of cognitive skills on learning, an app is most likely to support learning if it is delivered in a manner consistent with the patient’s cognitive skills (eg, abstract reasoning, and executive functioning skills such as planning, implementing, and reflecting) and presented in a way that is meaningful. To this end, the proposed app will be designed to enable analytics for ongoing improvement and customization for different patterns of cognitive strengths and challenges compared with others (cognitive profiles) [44,45].

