#### Measures

At pretreatment, as in Phase 2, we will assess (1) demographic characteristics and comfort with technology to characterize the sample, and (2) cognitive skills to examine associations between cognitive profiles and homework completion as well as user experience.

During treatment, homework completion will be assessed weekly. The quantity (amount) as well as the quality (appropriateness) of homework will be assessed, based on evidence that they both relate to treatment outcome [99]. Multiple sources of homework information (adolescent, therapist, data logged by the app) will be obtained to address potential differences between sources [99,100]. Adolescents will assess the quantity and quality of their homework upon arriving at the session, by rating on a 5-point scale how much of it was completed and how well it was done, using 2 items from the Homework Rating Scale II [101], an internally consistent measure of homework quantity and quality developed for use with adults [102]. The 2 items have not previously been tested with adolescents and will be pilot-tested in this study. Two additional measures of homework quantity will be obtained by asking adolescents to estimate the number of days and the number of hours they spent doing homework [103]. Therapists will assess homework completion following the session. They will assess homework quantity by rating the proportion of assigned homework that was completed (from 0% to 100%), a method used in previous research [36,103]. They will rate the quality of the work on a 6-point scale [104], using criteria specified for each assignment; this measure has been found to predict treatment outcome [103]. A third source of information about homework quantity will be obtained in the app group from data logged by the app: the proportion of the task completed, the time spent on the task, and the number of visits to the assignment page.

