At pre, post, and each follow-up, treatment outcomes will be assessed. Anxiety and depression will be assessed using the same instruments as in Phase 2: the Achenbach Scales, which assess general symptomatology as reflected in internalizing problems, and externalizing problems, which often co-occur with anxiety and depression [105], the MASC-2, the CDI-2, and the ADIS. Other outcomes also will be assessed. Maladaptive cognitions will be assessed using the Children’s Automatic Thoughts Scale [106], in which youth rate the frequency over the past week of a set of 40 self-statements describing negative thoughts about physical threats, social threats, personal failure, and hostile intent. Quality of life will be assessed by the Pediatric Quality of Life Inventory [107,108], in which youth rate 23 self-statements assessing physical, emotional, social, and school functioning.

At posttreatment, a usability evaluation will be conducted with the app group (youth and therapists) following completion of the posttreatment assessment, using the same protocol as in Phase 2. To examine differences in client satisfaction between the app and no-app groups, will be assessed posttreatment (following the usability evaluation in the app group) via the Client Satisfaction Questionnaire (CSQ [109,110]), an 8-item global measure of satisfaction with service comprised of statements phrased as questions to be answered on a 4-point scale ranging from 1 (poor) to 4 (excellent). The CSQ is a well-established measure with good psychometric properties [110] that has been used in numerous studies with diverse patient samples, including children and adolescents in CBT [111,112]. Treatment fidelity will be assessed by an integrity-to-protocol checklist [113], which therapists will complete after each session. The checklist yields a proportion score reflecting the rate of adherence to the CBT treatment manual. Finally, health economic cost data will be obtained to assess cost-effectiveness of the app. Cost data will consist of technology costs, including detailed micro costing of the app program (eg, program costs, smartphone-related costs, server costs, maintenance), and the cost of time and other resources needed to integrate the app into routine clinical practice by therapists and clinics.

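### The exploratory mechanism analyses do not match their questions: the slope comparison can miss a homework-independent app effect, and the app-group mediation chain reverses the article's own theory

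*Protocol article*

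**What the plan says.** The theory is set out in the introduction. The Role of Mobile Tools states: "We expect that the app will improve homework completion by supporting learning". Support for Practice and Learning adds that "there is a direct association between homework completion and outcomes of CBT for anxiety or depression across a wide age range". Together these give the order app, support for learning, homework completion, outcome.

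The Treatment Outcomes part of the Phase 3 data analysis then plans two analyses.

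- **Slope comparison.** If outcomes differ between groups, the article asks whether better homework or some other feature of the mobile technology is responsible. It examines homework-outcome associations separately in each arm. The regressions predict outcome from homework and the pretreatment value, and no arm term is mentioned. A difference in strength of association, it says, "would suggest that an improvement in homework completion is not the only mediator of app effects on treatment outcome".
- **Mediation.** If outcomes are better with the app, "exploratory mediation analyses will be performed for the app group", to assess "whether homework completion (quantity, quality) affects treatment outcomes indirectly through support for learning". Support for learning is defined as "ratings of how much the app supports access to assignments, memory and understanding of lessons, motivation to practice", followed by coaching, self-monitoring and review of homework.

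On timing, the Measures section says "During treatment, homework completion will be assessed weekly", and that at posttreatment "a usability evaluation will be conducted with the app group (youth and therapists) following completion of the posttreatment assessment".

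**The concern.** The first question is whether the app works by a route that does not pass through homework. That route shows as a difference between arms at the same level of homework. The planned comparison looks at a different quantity, namely whether the return on homework differs between arms. The two can come apart in both directions, so a real homework-independent effect may go unseen, and a slope difference may arise for reasons unrelated to another pathway.

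In the second analysis, the variable that the introduction treats as the cause of homework (support) is placed after it, as mediator. The indirect effect would then be estimated for a path that the article does not hypothesise. The mediator is also a rating given after treatment and after the posttreatment outcome assessment, so it may reflect how much the youth improved.

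At stake is what the trial reports about mechanism, and hence what developers and clinics conclude about why the app helps.

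**Working it through.** The article gives no effect sizes for these analyses, so there is no figure to reproduce. All effect sizes below are assumptions. Tests are two-sided at 0.05. The 50 per arm comes from the planned 100 youth and the 35 per arm from the power statement (Sample Size and Power).

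**1. Slope comparison when a homework-independent effect exists and slopes are equal.** Assumed model, in SD units of residual error:

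- homework H = 0.5 × arm + error
- outcome Y = 0.4 × H + d × arm + error

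The arm × homework coefficient is zero by construction, so the slope comparison rejects at about 5% whatever the size of d. Simulation gives 5.3%.

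For the arm coefficient adjusted for H:

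- squared correlation of arm and H: r² = (0.5² × 0.25) / (0.5² × 0.25 + 1) = 0.0625 / 1.0625 = 0.0588
- variance inflation: 1 / (1 − 0.0588) = 1.0625
- SE = √(2/n × 1.0625), which is 0.206 at n = 50 and 0.246 at n = 35 per arm

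| Direct effect d | d/SE, n = 50 | Power | d/SE, n = 35 | Power |
|---|---|---|---|---|
| 0.6 SD | 2.91 | 82% | 2.43 | 67% |
| 0.4 SD | 1.94 | 48% | 1.62 | 36% |
| 0.3 SD | 1.46 | 30% | 1.22 | 22% |

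Simulation agrees within about two percentage points. With the article's 10% attrition at each follow-up, 50 × 0.9 × 0.9 = 40.5 per arm would be assessed at 12 months, between the two columns.

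**2. Slope comparison when homework is the only pathway.** Simulated with 50 per arm, pretreatment value in the model, 4,000 trials:

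| Situation | Slopes differ | Arm effect given homework |
|---|---|---|
| No artefact, slope 0.8 | 5% | 5% |
| Homework measured with more error in the no-app arm (error SD 1.2 versus 0.2) | 65% | 11% |
| Diminishing returns (0.8H − 0.25H², app raises H by 1.2) | 74% | 4% |

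In the second row the observed slope shrinks by 1/(1 + 1.2²) = 0.41 in one arm and by 1/(1 + 0.2²) = 0.96 in the other, although the true slope is the same. The adjusted arm effect is also disturbed there, but much less.

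**3. Direction of the mediation chain.** The two statements side by side:

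- Introduction: support for learning → homework → outcome.
- Treatment Outcomes: homework → support for learning → outcome.

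Simulated in one arm of 50, with a joint-significance test and 1,500 trials:

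| Truth | Planned chain significant | Introduction's chain significant |
|---|---|---|
| Support → homework → outcome, both paths 0.5 | 5% | 87% |
| Same, homework measured with error (SD 1) | 10% | 37% |
| Support rating only a consequence of homework and improvement (0.4 each) | 87% | 36% |

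If the introduction is right, the planned test finds little. If the rating merely reflects having improved, the planned test is usually significant although support mediates nothing. In that last case the introduction's order is also significant too often, so reordering does not cure a rating collected too late.

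**4. Timing.** Homework is recorded weekly, and the usability evaluation follows the posttreatment assessment. It reuses the Phase 2 protocol, which also had weekly interviews. However, the six support items named for the mediation, including review of homework, match the list in the final Phase 2 interview. The weekly list does not include review of homework.

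**The case against.** **Is the slope rule invalid?** A reader might infer so and want the sentence deleted. The article does not support that reading. If homework were the only pathway, the relation linear and measurement error equal, outcome would depend on arm only through homework and the slopes would have to be equal. Unequal slopes are then real evidence against sole mediation, which is what the hedged sentence says. This stands: the rule is insensitive and fragile, not invalid.

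**Does the article claim that equal slopes rule out another route?** It does not. It draws an inference only from a difference. The criticism is that the comparison is the only analysis planned for the question and is silent when slopes are equal.

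**Is the 5% versus 82% contrast favourable by construction?** Yes. The 5% follows from assuming equal slopes and the 82% from a large direct effect. At smaller effects the adjusted test is weak too.

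**Is it an error to restrict mediation to the app group?** A reader might object that an arm effect cannot be mediated within one arm. But this analysis does not claim to mediate the arm effect, and ratings of what the app supports cannot exist without the app.

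**Can the planned order be defended?** Practice may itself produce learning, and for the 6- and 12-month outcomes the measurement order (weekly homework, posttreatment rating, later outcome) does fit the chain. But the rating describes what the app provides, which the introduction places before homework, and the fit fails for the posttreatment outcome. Simply reversing the chain with the same ratings would put the cause after its mediator.

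**Conclusion.** The point holds in two parts.

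1. The slope comparison alone does not answer whether the app has a homework-independent effect. With equal slopes it flags such an effect at about 5%, and slopes can also differ through differential measurement error or non-linearity. This follows from the model structure. The gain from an adjusted arm effect depends on assumed sizes: about 82% at 0.6 SD and 30% at 0.3 SD with 50 per arm and no attrition, and less with 35 per arm.
2. The app-group mediation chain reverses the introduction's theory, and its mediator is rated after the posttreatment outcome.

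A reader might infer that the trial's main conclusion is in doubt. It is not. Both analyses are labelled exploratory and run only if outcomes differ between groups, and the comparison of homework completion does not use them. What could mislead is the account of mechanism.

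**What to change.** **Slope question.** In all randomised youth, model arm → homework completion → outcome, adjusted for the pretreatment value and site, with an arm × homework term. Use the adolescent and therapist measures, since app-logged data exist in one arm only. Report the indirect effect and the remaining direct arm effect with confidence intervals, and state the homework level at which the direct effect is evaluated. State the assumption of no unmeasured confounding between homework and outcome, because homework is not randomised. Keep the slope comparison as a supplementary check. Add that equal slopes do not exclude another pathway, and that unequal slopes may reflect moderation, measurement error or non-linearity.

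**App-group mediation.** Test support → homework → outcome only if support ratings that precede the homework and outcome they explain are available. Otherwise report the posttreatment ratings as associations, not mediation.

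**Cost.** The two paragraphs on these analyses need rewriting. The first change uses data already planned in both arms. Testing the second chain would need earlier support ratings, for example weekly ones, if Phase 3 does not already collect them. Reporting associations costs nothing.
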